**Assessments:**								
Labour and Delivery			X	X	X			
Operative delivery					X			
Perineal outcome					X			
Blood loss					X			
Maternal complications					X	X		
Hospital stay					X			
Readmission						X		
Neonatal outcomes					X	X		
NICU admission(s)					X	X		
Satisfaction with birth						X		
Breast feeding						X	X	X
Health related quality of life						X	X	X
Pelvic floor						X	X	X
Depression						X	X	X

### Primary outcome

Mode of delivery will be ascertained from the medical records.

### Other outcomes

Labour and delivery outcomes, perineal trauma, blood loss, duration of hospitalisation, short-term neonatal outcomes, and admission to the neonatal intensive care unit, maternal or neonatal readmission to the same institution, and other components of the combined secondary outcomes will be ascertained by a study investigator not involved in clinical care, using the medical records recorded contemporaneously by the clinician and by contacting the participants’ clinician for further information if required. Maternal depression, health related quality of life (SF-12), birth satisfaction (VAS), maternal or neonatal readmission to another institution, ongoing breast feeding, pelvic floor symptoms and components of the combined secondary outcomes will be collected by structured maternal questionnaires at 6 weeks, 6 months and 12 months post-delivery as outlined in section 15. Questionnaires will be completed by mail-out, online via the trial website and by telephone depending on the participants’ preferences (Figure 1, Table 2). Data collectors will be unaware of the treatment allocation at all times.

As the primary outcome is mode of delivery and randomisation occurs during the second stage of labour, we expect 100% ascertainment for the primary outcome.

Study investigators will perform site visits about four times per year to promote recruitment, provide education for clinical staff and site investigators and to audit centre medical records to verify the accuracy of the data collected by the sites.

Each participants will receive a phone call at each time point by research staff not involved in her care to ask her preference for follow-up. Unless she declines further participation, each participant will receive a reminder phone call and will be offered completion of the questionnaire by telephone if they feel they cannot complete it by mail or online.

### Data management

Data collected will be entered into a registered electronic database by research staff blinded to treatment allocation and who are not involved in the clinical care of the participants. Hardcopies of participants’ data will be stored in a locked office. The electronic database will include the study identification number but no directly identifying data such as medical record number, date of birth or personal address. The de-identified database will be backed up on a server at Royal Prince Alfred Hospital. Data linking identifying details to the study number will be kept at a separate location in a locked filing cabinet. At the end of the study, data will be kept in a locked filing cabinet, and de-identified electronic data will be kept on a portable medium such as a USB drive in a separate secure location at Royal Prince Alfred Hospital.

All electronic data will be checked for accuracy by a second member of the research team and any apparent data entry errors will be discussed by the primary investigators and investigated/corrected as required.

### Analysis

Analysis will be by intention-to-treat (according to treatment allocation), including withdrawals and losses to follow-up. Losses to follow-up for the primary outcome are not expected because randomisation will occur at full dilatation and the primary outcome is the mode of delivery.

The results will be reported according to CONSORT guidelines.

Demographics and other potential confounders will be compared by treatment allocation in a univariate analysis. Categorical outcome measures will be compared by proportions (chi-squared test), means for normally distributed data (*t*-test), or rank order for non-normally distributed data (Mann–Whitney-*U* test).

A logistic regression analysis of treatment allocation and other variables on the primary outcome measure, operative delivery, will be performed. The following variables will be considered for the logistic regression model: maternal body mass index, maternal age, maternal height, maternal ethnicity, gestation, induction of labour, gestational diabetes, neonatal gender, and RCOG CTG classification in the second stage of labour. Parity, study site and the presence of epidural for intrapartum analgesia at the time of randomisation will not be included because randomisation is stratified for these variables. Only variables where *P* <0.25 in the univariate regression will be included in the multivariate model. Continuous variables that do not show a linear association with the logit function will be divided into quartiles and treated as categorical. Interaction terms will be considered for treatment allocation versus each of the other variables and where clinically appropriate between non-treatment variables. *P* <0.01 will be considered evidence of interaction. Terms will be excluded from the model in a stepwise backward manner until all remaining terms are both statistically significant (*P* <0.05) and clinically significant (that is, removal of the term results in a clinically significant change in the estimate of the odds ratio of treatment allocation for the primary outcome). The analysis will be performed using SAS 9.2 (or a more recent version of SAS).

Subgroup analyses will be performed according to the technique of manual rotation employed (manual/whole hand versus digital/fingers) and according to operator ability (data will be divided into two approximately equal groups according to the success rate of the operator who performed the manual rotation).

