**Methods/Design:**

Eligible participants will be (greater than or equal to) 37 weeks’ with a singleton pregnancy and a cephalic presentation in the occiput posterior position on transabdominal ultrasound early in the second stage of labour. Based on a background risk of operative delivery of 68%, then for a reduction to 50%, an alpha value of 0.05 and a beta value of 0.2, 254 participants will need to be enrolled.

This study has been approved by the Ethics Review Committee (RPAH Zone) of the Sydney Local Health District, Sydney, Australia, and protocol number X110410.

Participants with written consent will be randomised to either prophylactic manual rotation or a sham procedure. The primary outcome will be operative delivery (defined as vacuum, forceps and/or caesarean section deliveries). Secondary outcomes will be caesarean section, significant maternal mortality/morbidity and significant perinatal mortality/morbidity.

Analysis will be by intention-to-treat. Primary and secondary outcomes will be compared using a chi-squared test. A logistic regression for the primary outcome will be undertaken to account for potential confounders.

The results of the trial will be presented at one or more medical conferences. The trial will be submitted to peer review journals for consideration for publication. There will be potential to incorporate the results into professional guidelines for obstetricians and midwives.

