### The timing of the intervention

The intervention will begin once full dilatation has been diagnosed and the woman has the first urge to push or after one hour, whichever occurs first.

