### Randomization/allocation concealment

Randomization will be stratified by parity, hospital site and epidural due to the potentially strong association between operative delivery (the primary outcome) and each of these factors. Randomization will be centrally controlled using computerized sequence generation, which can be accessed 24 hours per day using a toll-free telephone line.

In order to reduce the risk of randomising an ineligible participant, randomisation will occur immediately before the intervention or sham procedure is to be performed. An example of a participant becoming ineligible would be if the fetus rotated from the occiput posterior to occiput transverse position. Each investigator will complete a data collection form at the time the manual rotation or sham procedure is performed outlining the treatment allocation, clinical findings, and whether or not the fetus was successfully rotated.

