**An overview of the conduct of the POP-OUT Trial.**

AntenatallyIn the latent phase of labourIn the active phase of the first stage of labour, with an effective epidural anaesthesia

An ultrasound will be performed at full dilatation by the clinician caring for the woman and the findings will be recorded on a data sheet immediately afterwards.

An hour after full dilatation or at the first urge to push, a study investigator (with no clinical responsibility for the woman in the trial) will confirm the OP position by a second (pre-procedure) bedside ultrasound. If the fetal position is still OP and the woman still wishes to participate, then the study investigator will randomise the woman to either manual or sham rotation. The treatment allocation will be recorded on a randomisation sheet that the investigator will keep on their person and not show to any of the participant’s carers.

After the manual rotation or sham has been performed the ultrasound will be repeated, ensuring that the woman and her carers do not see the screen. The investigator will leave and the woman will have her usual care from this point onwards. The investigator will record the findings of the vaginal examination he/she performed before the procedure, details of the procedure and post-procedure ultrasound findings on the same data sheet as the pre-procedure ultrasound. The study investigator will also keep this data sheet on their person and not show it to any of the participants’ carers.

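### The second-stage CTG covariate is not limited to readings before randomisation, so the adjusted logistic analysis can condition on a variable that treatment may have changed

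*Protocol article*

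**What the plan says.** The *Analysis* section names nine candidate covariates for the logistic model of the primary outcome. The list ends with "neonatal gender, and RCOG CTG classification in the second stage of labour". The next sentence leaves out the stratification factors and gives one of them a time point: "the presence of epidural for intrapartum analgesia at the time of randomisation". The CTG variable has none.

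Other sections fix when allocation happens:

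- *Other outcomes* (under data collection): "randomisation occurs during the second stage of labour".
- *Randomization/allocation concealment*: "randomisation will occur immediately before the intervention or sham procedure is to be performed".
- *The timing of the intervention* (Methods): the procedure starts "once full dilatation has been diagnosed and the woman has the first urge to push or after one hour", whichever comes first. *Study conduct* gives the same timing for the pre-procedure ultrasound and randomisation: "An hour after full dilatation or at the first urge to push, a study investigator".

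Candidates enter the multivariable model if P < 0.25 in univariate regression. Backward elimination then continues until every remaining term has P < 0.05 and is also clinically significant, meaning that "removal of the term results in a clinically significant change in the estimate of the odds ratio of treatment allocation".

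The abstract also plans an unadjusted comparison: "Primary and secondary outcomes will be compared using a chi-squared test".

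**The concern.** A covariate in a randomised comparison should be fixed before allocation. Once the procedure has been done, anything on the trace may be partly a result of it. If rotation affects the fetal heart rate, for example through the length of the second stage, CTG class lies between treatment and outcome. Adjusting for it then estimates something other than the total effect of rotation on operative delivery.

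The elimination rule adds to this. A true baseline variable is balanced by randomisation in expectation, so removing it changes the treatment odds ratio only through chance imbalance and non-collapsibility. A mediator differs systematically between arms and can change the odds ratio for that reason. Selecting on change in the treatment estimate therefore tends to favour the kind of variable that should stay out.

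At stake is the adjusted estimate for the primary outcome, which may be reported beside the unadjusted one and disagree with it.

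**Working it through.** **1. Timing.** The second stage begins at full dilatation. Randomisation follows at the first urge to push or after an hour, the procedure comes at once, and the second stage then runs on until delivery. A second-stage CTG can thus be read before or after treatment, and the covariate definition allows both. The other eight candidates (BMI, age, height, ethnicity, gestation, induction, gestational diabetes, sex of the baby) are settled before randomisation.

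**2. The plan's own figure.** *Sample size* gives 68% against 50%, two-sided alpha 0.05 and power 80%. The two-proportion formula gives 116.01 per group (117 when rounded up) without continuity correction:

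n = [1.960·√(2·0.59·0.41) + 0.842·√(0.68·0.32 + 0.50·0.50)]² / 0.18²

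With the correction n/4·[1 + √(1 + 4/(n·0.18))]² it gives 126.88, so 127 per group and 254 in total. This matches the plan. The calculation is for an unadjusted comparison and does not involve CTG.

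**3. Target effect.** Risk difference 50 − 68 = −18 points. Odds ratio (0.50/0.50)/(0.68/0.32) = 0.471.

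**4. Illustration.** *From the documents:* the marginal risks of 68% (sham) and 50% (rotation). *Assumed:* a binary abnormal CTG, its prevalence q in each arm, and its odds ratio of 3 to 5 for operative delivery.

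Model: logit P(operative) = b_arm + c·CTG, with c = ln(CTG odds ratio). For each arm, b is solved so that

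q·expit(b + c) + (1 − q)·expit(b) = 0.68 (sham) or 0.50 (rotation).

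The adjusted odds ratio is exp(b_rotation − b_sham). The adjusted risk difference applies the stratum risks of each arm to the pooled CTG prevalence, (q_sham + q_rotation)/2.

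*Worked case: abnormal CTG 40% sham, 25% rotation, CTG odds ratio 3.*

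- b_sham = 0.370 and b_rotation = −0.265.
- Sham risks: 59.1% with normal CTG, 81.3% with abnormal CTG.
- Rotation risks: 43.4% and 69.7%.
- Pooled prevalence 32.5%. Sham: 0.325·81.3 + 0.675·59.1 = 66.3%. Rotation: 0.325·69.7 + 0.675·43.4 = 52.0%.
- Adjusted risk difference −14.4 points (from unrounded values).

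| Abnormal CTG, sham → rotation | Adjusted OR (CTG OR 3 to 5) | Adjusted risk difference, points |
|---|---|---|
| 40% → 40% (no effect) | 0.45 to 0.42 | −18.0 |
| 40% → 35% | 0.47 to 0.46 | −16.8 to −16.3 |
| 40% → 25% | 0.53 to 0.55 | −14.4 to −13.0 |
| 25% → 40% | 0.38 to 0.34 | −21.6 to −22.9 |

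**5. Which scale to read.** With no effect on CTG the adjusted odds ratio is already 0.42 to 0.45 rather than 0.47. That gap is non-collapsibility, not bias. Setting an adjusted odds ratio against 0.47 mixes the two, so the risk difference is the fairer measure.

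**The case against.** The strongest reply is that the wording does not make the covariate post-randomisation. A second-stage reading before allocation exists, and the same RCOG classification is used in an exclusion criterion, so the authors may well have meant a baseline value. The abstract describes the regression as accounting for confounders, which fits that reading. This stands: the defect is a missing time anchor, not a stated choice of post-treatment data. It does not dispose of the point, because epidural is anchored in the very next sentence, and because the article fixes the covariate list and the retention rule itself rather than leaving them to another document.

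The second reply is that the main comparison is safe. This also stands. The chi-squared test uses no covariates, and CTG enters the regression only if it passes the screening and elimination steps.

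Three stronger readings are tempting but not supported:

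- *That the protocol itself says rotation disturbs the CTG.* The section on discontinuing the intervention mentions fetal compromise for the intervention or the sham alike and attributes nothing to rotation. No section reports an effect of rotation on CTG.
- *That CTG is the candidate most likely to survive selection.* The documents give no predictor strengths for any candidate. In the 40% → 35% case the adjusted odds ratio hardly moves from 0.471, because mediation and non-collapsibility offset each other, so the rule might drop the term.
- *That adjustment would shrink the effect.* It would do so only if rotation improves CTG; if rotation worsens it, the effect is exaggerated.

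**Conclusion.** The point holds as a defect in the definition of one candidate covariate. The text admits CTG recorded after randomisation into the adjusted model, and the retention rule leans towards keeping a variable on the treatment pathway.

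Under the assumed CTG odds ratios of 3 to 5, the distortion of an 18-point reduction is about 1 to 2 points for a 5-point fall in abnormal CTG and about 4 to 5 points for a 15-point shift in either direction. It is nil if rotation does not affect CTG. The prevalences, the shifts and the odds ratios are all assumptions. The illustration also leaves out unmeasured common causes of CTG and mode of delivery, which could add a further bias that was not calculated.

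A reader might infer that the trial's primary result is compromised. It is not: the unadjusted intention-to-treat comparison and the sample size of 254 do not depend on this covariate. The change is worth making, but it does not threaten the trial.

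**What to change.** In *Analysis*, define the covariate as the last RCOG CTG classification recorded before randomisation, or remove it from the list. State that no CTG information recorded after randomisation enters the effectiveness model.

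The exclusion criterion already requires an RCOG classification before randomisation. Table 2 places the second eligibility screen in the first stage of labour, so the time of the reading used should be recorded with it.

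The cost is a few words and one time-stamped field. The sample size, the chi-squared comparison and clinical care do not change. The definition should be settled before allocation is revealed for analysis.

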### Primary objectives

The primary objectives are to determine the differences between intervention and control groups in the operative delivery rate (defined as vacuum, forceps and/or caesarean section deliveries).

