### Trial design

The POP-OUT trial is designed as a superiority, double-blinded, multicentre, randomised controlled clinical trial with two parallel groups and a primary endpoint of operative delivery. Randomization will be performed as block randomization with a 1:1 allocation.

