### Sample size

The sample size (254) was calculated on the basis of the primary outcome. The power calculation was based on our prospective cohort study of 160 women that was completed in May 2009 [3] and showed an operative delivery rate of 68% in the OP group, and from our survey of obstetricians conducted in 2010, who indicated they would perform a manual rotation for OP position if it reduced the rate of operative delivery from 68% to 50% [10]. To detect a reduction in the rate of operative delivery from 68% in the control group to 50% in the intervention group, a sample size of 127 women in each group (total = 254) will be required to have 80% power of finding a result. Alpha = 0.05 (2-tailed), Beta = 0.20 (Epi-Info version 3.3.2).

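### The treatment-interaction search inside the adjusted logistic model can leave operative delivery without an overall adjusted odds ratio

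*Protocol article*

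**What the plan says.** The protocol article's Primary objectives section asks for one overall contrast: "The primary objectives are to determine the differences between intervention and control groups in the operative delivery rate". The Abstract (Methods/Design) compares outcomes by chi-squared test and adds a logistic regression of the primary outcome to deal with confounding.

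The Analysis section then sets out how that regression is built:

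- **Candidates.** Nine variables: BMI, age, height, ethnicity, gestation, induction, gestational diabetes, the baby's sex and CTG class. Only those with univariate P<0.25 enter the multivariable model.
- **Interactions.** "Interaction terms will be considered for treatment allocation versus each of the other variables and where clinically appropriate between non-treatment variables", with the criterion that "P* <0.01 will be considered evidence of interaction".
- **Elimination.** "Terms will be excluded from the model in a stepwise backward manner until all remaining terms are both statistically significant" at P<0.05 and also clinically significant. The second condition means that dropping the term must change the treatment odds ratio by a clinically important amount; no amount is given.

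None of the nine is put forward as an effect modifier. The planned subgroup analyses, by rotation technique and by operator success rate, are listed separately. The section does not say that an overall adjusted odds ratio will still be reported if a treatment interaction stays in the model.

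**The concern.** One model is given two jobs: estimating the adjusted overall effect and searching for effect modification. These conflict as soon as a treatment interaction is retained, because the treatment coefficient then describes women at one level of the covariate, not the trial population. The plan's own retention test also loses its reference quantity.

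At stake is the confounder-adjusted answer to the primary question. The chi-squared test would report an overall effect while the adjusted analysis reported level-specific ones, so a reader could not use one to check the other. With 254 women and no interaction hypothesised in advance, a retained interaction could easily be a chance finding.

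**Working it through.** **1. The plan's own figure.** Inputs from the Sample size and Trial design sections: "To detect a reduction in the rate of operative delivery from 68% in the control group to 50% in the intervention group"; two-sided alpha 0.05, power 80%; 1:1 allocation.

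Uncorrected n per arm = [1.960 × √(2 × 0.59 × 0.41) + 0.842 × √(0.68 × 0.32 + 0.50 × 0.50)]² / 0.18² = (1.363 + 0.576)² / 0.0324 ≈ 116.0, rounded up to 117.

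With continuity correction: (116.0/4) × [1 + √(1 + 4/(116.0 × 0.18))]² ≈ 126.9, rounded up to 127.

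This matches the stated "a sample size of 127 women in each group (total = 254) will be required". The calculation compares two proportions, with no regression model, so the interaction search cannot affect it.

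**2. What a retained interaction does.** Write the model as logit(p) = a + bT + cX + dTX, with T the treatment and X a covariate. The treatment odds ratio at X = x is exp(b + dx). With d = 0 it is exp(b) for everyone; with d ≠ 0 there is a different odds ratio for each x. Shifting the origin of X by m changes the treatment coefficient from b to b + dm without changing the fit. Whether removing the TX term changes the treatment odds ratio importantly therefore depends on how X was coded, and the rule as written does not settle it.

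**3. Chance of at least one false treatment interaction, independent tests at 0.01.** The formula is 1 − 0.99^k.

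| Variables tested, k | Chance |
|---|---|
| 9 | 8.6% |
| 5 | 4.9% |
| 3 | 3.0% |

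Nine is the ceiling. If no covariate is prognostic, each passes the P<0.25 screen with probability 0.25, so on average 9 × 0.25 ≈ 2.3 remain. Averaging over the number kept gives 1 − (0.75 + 0.25 × 0.99)^9 = 1 − 0.9975^9 = 2.2%.

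**4. Simulation at the planned size.** 254 women, 1:1, 68% versus 50%, no true interaction, 3,000 runs per scenario. Each treatment-by-covariate term was tested by a 1-df likelihood-ratio test at 0.01. Assumed, not from the protocol: four standard-normal covariates, five binary ones (prevalences 0.35, 0.40, 0.10, 0.50, 0.30), all independent. In the prognostic scenario each covariate has a log-odds effect of 0.25 per standard deviation.

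| Scenario | Mean variables tested | At least one false interaction |
|---|---|---|
| No screen, none prognostic | 9.0 | 10.2% |
| Screen, none prognostic | 2.3 | 3.0% |
| Screen, moderately prognostic | 6.4 | 6.5% |

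The simulation standard error for the first row is √(0.102 × 0.898/3000) = 0.55 percentage points.

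**5. How far the second retention condition helps.** Taking a 10% shift in the treatment odds ratio as the cut-off (an assumption), every false interaction with a 0/1-coded covariate met it. Of those with a mean-centred continuous covariate, 10–16% did. Over all covariates, 58% to 71% of false interactions met it, depending on the scenario. The condition removes some hits, but coding largely decides which.

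**The case against.** The strongest reply is that the primary objective is answered elsewhere. The chi-squared comparison gives one overall result that no interaction can change, and the trial was sized for it. This is right, and it confines the point to the adjusted analysis. A reader might infer that a chance interaction could displace the trial's main result; the protocol does not support that.

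Three other strong readings also fail.

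- **That any interaction below P<0.01 is kept.** It must also meet the clinical-significance condition and, on the natural reading, involve a variable that passed the screen. Both reduce the risk, though the first is undefined and depends on coding.
- **That the P<0.01 and P<0.05 thresholds contradict each other**, so that interactions could be judged at 0.05 (37% for nine tests, 1 − 0.95^9). The text can be read with the specific rule governing interactions and the general rule governing other terms, so the 0.05 figures do not describe a rule the plan must be taken to use.
- **That the treatment coefficient would often have the wrong sign.** In a separate simulation of 4,000 trials under assumed distributions, 116 of 371 hits (31%) did so with covariates in raw units, but only 4 of 371 (1.1%) at the covariate mean. Most of the raw figure (82 of 116) comes from reading the effect at a continuous covariate's value of zero. The protocol does not say that coefficient would be reported as the effect.

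It can also be said that presentation of a retained interaction belongs in an analysis plan, and nothing here says one would become a subgroup claim. That holds for presentation. It does not cover the stated model-building rule, which puts treatment interactions into the elimination and judges terms by an odds ratio that such an interaction removes.

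**Conclusion.** The point stands in limited form. In the supportive adjusted analysis, the stated procedure can retain a treatment interaction that nobody hypothesised. If it does, no single adjusted treatment odds ratio remains, and the retention rule cannot be applied unambiguously.

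With no true interaction, the chance of at least one false treatment interaction at P<0.01 is at most about 9–10% with all nine variables tested, and roughly 2–7% after the screen. These are rates of reaching P<0.01; the clinical-significance condition would lower the rate of retention by an amount that cannot be fixed without a cut-off. The 8.6% and 2.2% figures assume independent tests, and the simulated figures rest on assumed covariate distributions and effects. The algebra in step 2 of the working needs none of these assumptions.

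The risk is modest and does not reach the chi-squared test, the power or the sample size. The change is still worth making because it costs almost nothing and secures the adjusted estimate of the overall effect.

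**What to change.** In the Analysis section, replace the treatment-interaction rule with wording to this effect: the adjusted treatment effect on operative delivery is estimated from a main-effects model containing no treatment-by-covariate interaction, and this estimate is always reported; treatment-by-covariate interactions are not part of the backward elimination; they are examined in separate exploratory models, reported with the number tested, and do not alter the overall adjusted estimate.

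Interactions between two non-treatment covariates do not make the treatment coefficient level-specific, so this change need not touch them.

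The change is to wording only, with no extra data or participants. The Trial status section reports 160 recruited of the planned 254 and no interim analysis is planned, so it can be made through the stated amendment route before outcomes are compared by arm. The downside is that a genuine interaction would be labelled exploratory, which is reasonable in a trial sized only for the overall difference.
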